#### Examinations during treatment in week 24 and 48, at the end of hepatitis C therapy/documentation and in week 24 of follow-up

- Metabolic syndrome

**Definition according to WHO (1999):**

*Glucose intolerance, impaired glucose tolerance (IGT) or diabetes mellitus and/or insulin resistance together with two or more of the other criteria listed below:*

Criteria:

- Impaired glucose regulation or diabetes
- Insulin resistance (highest quartiles of the HOMA-IR index)
- Dyslipidemia:

Triglycerides:  150 mg/dl (1.7 mmol/l) and/or

HDL cholesterol: ♂:< 35 mg/dl (0.9 mmol/l), ♀: < 39 mg/dl (1.0 mmol/l)

- Hypertension: ≥ 140/90 mm Hg and/or corresponding treatment
- Central obesity: waist-to-hip ratio: ♂: > 0.9, ♀: > 0.85 and/or BMI > 30 kg/m2

Microalbuminuria: ≥ 20 µg/min or ≥ 30 mg/g creatinine (albumin-to-creatinine ratio)

or

**Definition acc. to NCEPIIIATP (2001) synonym ATP III:**

Criteria:

- Hypertriglyceridemia:  150 mg/dl (1.7 mmol/l)
- Lowered HDL cholesterol: ♂:< 40 mg/dl, ♀: < 50 mg/dl
- Hypertension: ≥ 130/85 mm Hg and/or corresponding treatment
- Central obesity: BMI > 30 kg/m2 or waist: ♂: > 102 cm, ♀: >88 cm

Elevated fasting plasma glucose: ≥ 110 mg/dl (6.1 mmol/l)

or

**Definition acc. to IDF (2005):**

*Central obesity defined as: waist: ♂: > 94 cm (European), ♀: >80 cm (European) + 2 of the following criteria*

*Central obesity defined as: waist: ♂: > 90 cm (Asian), ♀: >80 cm (Asian) + 2 of the following criteria*

*Central obesity defined as: waist: ♂: > 85 cm (Japanese), ♀: >90 cm (Japanese) + 2 of the following criteria*

*For South and Central Americans the values for Asians are used.*

*For Africans, Mediterranean inhabitants and inhabitants of the Middle East the values for Europeans are used.*

Criteria:

- Hypertriglyceridemia:  150 mg/dl (1.7 mmol/l) or corresponding treatment
- Lowered HDL cholesterol: ♂:< 40 mg/dl (0.9 mmol/l), ♀: < 50 mg/dl (1.1 mmol/l) or corresponding treatment
- Hypertension: ≥ 130/85 mm Hg or corresponding treatment
- Elevated fasting plasma glucose: ≥ 100 mg/dl (5.6 mmol/l) or type 2 diabetes
- Diabetes mellitus type ???
- Overweight
- Blood pressure parameters
- Hip and waist circumference (calculation of hip/waist ratio)
- Smoker:
  1. currently smoking: patients who have previously smoked ³ 100 cigarettes and are currently smoking.
  2. former smokers: patients who have previously smoked ³ 100 cigarettes and are currently not smoking.
  Nonsmokers:
  patients who have previously smoked < 100 cigarettes.
- Laboratory parameters:
  Na, K, Ca, insulin (fasting)
  (Calculation of the HOMA-IR index:
  [fasting insulin (in mIU/l) x fasting plasma glucose (in mmol/l)/ 22.5]
  or
  [fasting insulin (in mIU/l) x fasting plasma glucose (in mg/dl)/ 405]),
  (repeat presentation of HbA1c, HDL, LDL, triglycerides, cholesterol (total), glucose (fasting), uric acid, BMI)
- Special concomitant medication

Diabetes: insulins and insulin analogues, oral antidiabetics (e.g. alpha-glucosidase inhibitors, biguanide derivatives, sulfonylurea derivatives, "glinides", "glitazones")

Hypertension: antihypertensives (e.g. ACE inhibitors, angiotensin II antagonists, centrally acting antihypertensives, beta receptor blockers, calcium channel blockers, diuretics, combination products)

Dyslipidemia: lipid reducers (e.g. HMG-CoA reductase inhibitors, fibrates, nicotinic acid and derivatives),

Obesity: e.g. lipase inhibitors, appetite suppressants

### Additional module to record treatment of hepatitis C in patients after liver transplant

#### Baseline examination: transplant-related data

- - - - 1. *Information on donor*
- Gender, age, height, body weight, CMV (positive/negative/NA), HBV (HBsAg, anti-HBc), anti-HCV
- Donor organ quality (good, acceptable, poor); perfusion (excellent, good, acceptable, poor).
  - - - 1. *Information on recipient*
- History of primary liver disease ([selection fields: alcoholic liver disease, PBC, PSC, hepatitis B, hepatitis C, hepatitis of undetermined etiology, fulminant liver failure/toxic hepatitis, HCC, AIH, other (specify)]
- Blood group: 0, a, B, aB; Rhesus +/-
- Concomitant malignancies: HCC (yes/no)
- Specific laboratory data to calculate the MELD score before transplantation ((S-creatinine, INR, bilirubin before transplantation) 10*(0.957ln (serum creatinine)+0.378Ln (bilirubin total)+1.12ln(INR)+0.643)
- Anti-HAV (anti-HAV (IgG / IgM) negative)
- CMV status on liver transplantation (positive, negative), CMV prophylaxis/treatment [selection fields for duration]
  - - - 1. *Information on transplantation/allocation*
- Date and type of liver transplantation (LDLT, split, full-size organ); (first or retransplantation (date, cause (rejection, cirrhosis, other)), combined/other transplantation, cold ischemia time (0-30 hours)
- Initial immunosuppressive regimen in liver transplantation [selection fields: tacrolimus, cyclosporines, mycophenolate mofetil, azathioprine, sirolimus, everolimus, methylprednisolone, prednisolone, prednisone, hydrocortisone, other (specify)] including induction therapy, if any [selection fields: none, IL-2 receptor inhibitors, ATG/ATGAM/ALG, OKT3, other (specify)]
  - - 1. ***Baseline examination: Evaluation between liver transplantation and start of peg­interferon alfa-2a +/-ribavirin treatment***
- Smoking behaviour (see cardiovascular module, fade in if necessary or enter appropriately)
- Hepatitis C laboratory diagnostic tests: HCV-PCR (qualitative/quantitative), anti-HCV (last status in each case)
- CMV disease since liver transplantation up to start of peg­interferon therapy: number; viral load (PCR system), CMV syndrome, tissue invasive CMV infection; CMV prophylaxis / CMV therapy / both / no treatment
- Acute cellular rejection since liver transplantation: number, highest Banff score, highest rejection activity score, treated yes/no
- Chronic ductopenic rejection since liver transplantation:
  - ultrasound: normal findings, splenomegaly, picture of chronic liver disease, fatty liver, sonographic signs of liver cirrhosis, result not known, because performed by previous care physician
  - Histology: date of performance; stage of fibrosis and degree of inflammatory activity after selection of score
  - Fibroscan (kPa)
- Complications since liver transplantation (inquire with yes/no): bile duct stenoses (NAS/AS; ITBL), hepatic artery thrombosis, portal vein thrombosis, recurrent alcohol abuse, recurrent autoimmune mediated diseases (AIH, PBC, PSC)/ de novo AIH, HCC recurrence; HBV recurrence)
- Dialysis dependence (yes/no)
- Blood pressure parameters
- Current immunosuppressive therapy (generic names, daily dose, level)

Selection: mycophenolate mofetil, tacrolimus, cyclosporine, azathioprine, sirolimus, everolimus, prednisone, methylprednisone, prednisolone, hydrocortisone, other

For all, daily dose,

possible ranges

|  | Daily dose | Trough level |
| --- | --- | --- |
| Mycophenolate mofetil | 250 mg – 4 g | 0.5-5 mg/l |
| Tacrolimus | 5-30 mg | 3-20 ng/ml |
| Cyclosporine | 100 mg – 1 g | 30-500 ng/ml |
| Azathioprine | 50-300 mg | NA |
| Sirolimus | 3-15 mg | 3-20 ng/ml |
| Everolimus | 0.5-3 mg | 2-15 ng/ml |
| Prednisone, methyl­prednisone, prednisolone, hydro­cortisone | 1-100 mg | NA |

- Special concomitant medication:
  Erythropoietin, granulocyte stimulating factors, thrombopoietin
- Opportunistic infections in the last 52 weeks, pathogens involved: Aspergillus, Candida, Cryptococcus, herpes simplex, herpes zoster, Listeria monocytogenes, Pneumocystitis carinii, NA infection, no detectable pathogens
  - - 1. ***Examinations during hepatitis C treatment in week 12, 24, 36 and 48, at the end of hepatitis C treatment and*** ***in week 24 of follow-up***
- Dialysis dependence
- Blood pressure parameters
- Laboratory parameters
  Cholesterol, HDL, LDL, uric acid, albumin

For visit current immunosuppressive treatment (generic names, daily dose, level); selection: mycophenolate mofetil, tacrolimus, cyclosporine, azathioprine, sirolimus, everolimus, prednisone, methylprednisone, prednisolone, hydrocortisone, other

For all: daily dose

possible ranges

|  | Daily dose | Trough level |
| --- | --- | --- |
| Mycophenolate mofetil | 250 mg – 4 g | 0.5-5 mg/l |
| Tacrolimus | 5-30 mg | 3-20 ng/ml |
| Cyclosporine | 100 mg – 1 g | 30-500 ng/ml |
| Azathioprine | 50-300 mg | NA |
| Sirolimus | 3-15 mg | 3-20 ng/ml |
| Everolimus | 0.5-3 mg | 2-15 ng/ml |
| Prednisone, methylprednisone, prednisolone, hydrocortisone | 1-100 mg | NA |

- Special concomitant medication:
  Erythropoietin, granulocyte stimulating factors, thrombopoietin
- CMV infections, viral load (PCR system) and medication (prophylaxis, including duration, early therapy, therapy)
- Opportunistic infections pathogens involved: Aspergillus, Candida, Cryptococcus, herpes simplex, herpes zoster, Listeria monocytogenes, Pneumocystitis carinii, NA infection, no detectable pathogens
- Acute cellular rejection since liver transplantation: number, highest Banff score, highest rejection-activity score, treated yes/no
- Chronic ductopenic acute rejection since liver transplantation:
  - ultrasound: normal findings, splenomegaly, picture of chronic liver disease, fatty liver, sonographic signs of liver cirrhosis, result not known
  - Histology: date of performance; stage of fibrosis and degree of inflammatory activity after selection of score
  - Fibroscan (kPa)
- Loss of transplant yes/no, reasons:
- acute rejection
- chronic ductopenic rejection
- recurrence of underlying disease
- death with functioning transplant

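### The graft-loss item in the liver transplant module has no reason for vascular, biliary or de novo autoimmune loss and no 'other', so its cause table will be incomplete or misclassified unless reconciled with adverse event records

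*Protocol*

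**What the plan says.** Protocol 7.2.6 has a pre-treatment part and an on-treatment part.

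The pre-treatment part is headed "Baseline examination: Evaluation between liver transplantation and start of" peginterferon. It contains a yes/no item: "Complications since liver transplantation (inquire with yes/no): bile duct stenoses (NAS/AS; ITBL), hepatic artery thrombosis, portal vein thrombosis, recurrent alcohol abuse", continuing with "recurrent autoimmune mediated diseases (AIH, PBC, PSC)/ de novo AIH, HCC recurrence; HBV recurrence".

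The later part is headed "Examinations during hepatitis C treatment in week 12, 24, 36 and 48, at the end of hepatitis C treatment and" at follow-up week 24. It does not repeat the complications item. It does ask about rejection ("Acute cellular rejection since liver transplantation: number, highest Banff score, highest rejection-activity score, treated yes/no", and chronic ductopenic rejection), CMV and opportunistic infections, ultrasound, histology and Fibroscan. It closes with "Loss of transplant yes/no, reasons" and four reasons: acute rejection, chronic ductopenic rejection, "recurrence of underlying disease", and death with a functioning graft. No 'other' is offered.

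Two further sections matter. Section 7.4 has all adverse events documented through follow-up, but only up to 90 days after stopping for patients who discontinue prematurely. Sections 8.3 and 9 have all recorded variables presented descriptively, categorical ones as absolute and relative frequencies.

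**The concern.** A list of reasons without a residual category gives a valid cause distribution only if it is exhaustive. This one is not exhaustive by the module's own account: the baseline form names graft complications that the graft-loss item cannot express. A physician who records such a loss can leave the reason empty or choose the nearest code, most plausibly rejection or recurrence.

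What is at stake is the frequency table of graft-loss causes, which follows directly from the commitment to report every recorded variable. Section 4.2 says that earlier parts of the project made it possible to describe populations poorly represented in studies, and it asks for safety data to be recorded systematically. Transplant patients are such a population, so a reader would take this table at face value.

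**Working it through.** No sample size, power or event figure is involved. The check is a comparison of lists, then a comparison of two time windows.

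**Step 1. Baseline complications against graft-loss reasons (both 7.2.6).** Counting de novo AIH separately, the baseline item has eight entries.

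| Baseline entry | Graft-loss reason that could hold it |
| --- | --- |
| Bile duct stenoses | none |
| Hepatic artery thrombosis | none |
| Portal vein thrombosis | none |
| De novo AIH | none |
| Recurrent AIH, PBC or PSC | recurrence of underlying disease |
| HCC recurrence | recurrence of underlying disease |
| HBV recurrence | recurrence of underlying disease |
| Recurrent alcohol abuse | recurrence of underlying disease, if alcoholic liver disease was the indication |

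The last four can be coded because the primary-disease list in the recipient section of 7.2.6 contains each of those diseases. Result: 4 of 8 entries have no matching reason, and there is no 'other' to receive them.

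**Step 2. Is a closed list the protocol's normal practice?** No. In the same module the cause of retransplantation offers 'other', and primary liver disease and initial immunosuppression offer 'other' with specification. In the main module (7.2.2, end of treatment) the reasons for stopping therapy end with another-reason option. The graft-loss item departs from this pattern.

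**Step 3. Can other structured fields supply the cause?**
- Ultrasound on treatment (7.2.6): the categories contain no vascular or biliary finding.
- New comorbidities (7.2.2): asked at treatment visits and at end of treatment, but not in the follow-up list.
- Autoantibodies (7.2.2: week 24, end of treatment, follow-up) and histology (7.2.6): these bear on autoimmune disease but do not state why a graft was lost.
- Hospital admission reason (7.2.7): free text linked to SAE reports, limited to stays associated with the HCV disease or its therapy.
- Adverse events (7.2.8, 7.4): description, dates, seriousness, outcome and causality. This is the best source.

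**Step 4. Does the adverse event window cover the module window?** For patients who complete treatment it does, since 7.4 includes the follow-up phase. For patients who stop early:
- module window: 24 weeks × 7 = 168 days
- adverse event window: up to 90 days
- uncovered: 168 − 90 = 78 days

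This assumes that follow-up week 24 is counted from the end of treatment and that the early stopper still has that visit documented. A graft lost in those 78 days could then have a module entry and no adverse event description.

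**Step 5. How much can a new code still capture?** The current version is dated 28 February 2013 (Synopsis), and the inclusion period ran to 31 December 2011 (5.2). With about 72 weeks of documentation per patient (6.1), 72 × 7 = 504 days takes the last patient to 18 May 2013. With 72 weeks of treatment plus 24 weeks of follow-up, 96 × 7 = 672 days takes the last patient to 2 November 2013. The software rejects dates more than three months old (7.1). New codes therefore help only the last visits; earlier losses need reconciliation.

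**The case against.** The strongest reply is that the information exists elsewhere. A thrombosis, a biliary stenosis or the graft loss itself would be an adverse event, and a serious one if it met the criteria in 7.5, recorded with a description and dates. That is more than an undated yes/no item gives. This stands for most patients and is why the point is about reconciliation and coding rather than lost data. It does not stand for early stoppers after day 90.

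Four stronger readings are tempting, and the documents do not support them.

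- A reader might infer that graft complications are recorded only before treatment. Only the named complications item is confined to baseline. Rejection, alcohol use, autoantibodies, hepatitis B tests (where chronic hepatitis B was documented at baseline) and new comorbidities are all recorded on treatment or at its end.
- A reader might infer that none of the baseline complications can be coded as a cause of loss. Half can, as recurrence.
- A reader might infer that such losses are bound to be miscoded. The protocol does not say that the reason is compulsory or single-choice, and 7.2 says only that the parameters can be documented. Section 11 withholds payment for visits that stay incomplete after queries, which may favour an ill-fitting code over a blank, but it does not say that an empty reason makes a visit incomplete.
- A reader might infer that a planned comparison of complications before and during treatment is spoiled. Neither 4.2 nor 8.3 plans one, and the baseline item covers a variable, undated period since transplantation, so repeating it would not give comparable incidences.

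**Conclusion.** The point holds in a narrow form. As written, the graft-loss item cannot express vascular, biliary or de novo autoimmune loss. Its cause table will be incomplete or misclassified to the extent that such losses occur and are not reconciled with AE/SAE data. For patients who stop early, that reconciliation may find no adverse event record for up to 78 days of the module's follow-up, under the two assumptions stated in the working.

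No numerical magnitude can be given. The protocol states neither the number of transplant patients nor the number of graft losses nor their causes, so any percentage would only restate what was assumed. The consequence is limited to one descriptive table in a small subgroup module, and the main objective of efficacy and tolerability is unaffected.

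**What to change.** 1. Add 'vascular', 'biliary', 'de novo autoimmune' and 'other (specify)' to the graft-loss reasons in 7.2.6 for all remaining visits.
2. Before tabulating causes, reconcile every recorded graft loss, whatever reason was chosen or left blank, with the AE/SAE records. Query the site where no matching event exists, in particular for losses more than 90 days after premature discontinuation.
3. Report how many losses were reassigned and how many remain without a cause.

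Repeating the baseline complications item as new since the last examination is optional, because most of the relevant findings are already recorded on treatment and the rest should be reported as adverse events.

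The cost is a small eCRF change in one module and a few queries through the data-management process already described in 10.3.2. No extra examination is needed. Given the date of this version, the second step will do most of the work.

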### Pharmacoeconomics

- - - 1. ***Recording of scheduled visits***

For all visits scheduled according to the observational protocol, the following are recorded as appropriate:

- Date
- Physician contact yes/no*
- Contact with medical personnel yes/no**
- Complete blood count yes/no
- Basic blood count yes/no
- HCV-RNA determination qualitative yes/no
- HCV-RNA determination quantitative yes/no
- Determination of liver values yes/no
- Determination of thyroid values yes/no
- Determination of autoimmune antibodies yes/no
- Determination of HCV genotype yes/no
- Ultrasound
  - Normal ultrasound yes/no
  - Colour Doppler ultrasound yes/no
- Biopsy
  - Date
  - Outpatient/inpatient

Apart from the documentation of physician contact and contact with medical personnel, all data, as far as available, are taken from the main module. Additionally, the performance of an ultrasound examination (colour Doppler / normal), the determination of the thyroid values and the performance of a further liver biopsy can be reported for every visit of the main module.

*/** No differentiation is made between "visit" and telephone contact.

- - - 1. ***Recording of unscheduled visits***

For all visits held between the visits scheduled in the observational protocol, the following are recorded:

- Date period
- Physician contacts * (number)
- Contacts with medical personnel** (number)
- Complete blood count (number)
- Basic blood count (number)
- HCV-RNA determination qualitative (number)
- HCV-RNA determination quantitative (number)
- Determination of liver values (number)
- Determination of thyroid values (number)
- Ultrasound
  - Normal ultrasound (number)
  - Colour Doppler ultrasound (number)

*/** No differentiation is made between "visit" and telephone contact.

- - - 1. ***Recording of prescribed antiviral medication (hepatitis C)***
- Number of prescribed packs of Pegasys
  - Details of strength (135/180 µg)
  - Details of pack size (1/4/12 FS)
  - Details of date period of prescription
- Number of prescribed packs of Copegus
  - Details of strength (200/400 mg)
  - Details of pack size (28/42/112/168 (Copegus 200mg))
  - Details of pack size (14/56 (Copegus 400mg))
  - Details of date period of prescription
    - 1. ***Recording of prescribed concomitant medication (hepatitis C associated)***
- Number of prescribed packs of concomitant medication
  - Details of strength
  - Details of pack size
  - Details of date period of prescription
    - 1. ***Recording of prescribed HIV medication***
- Number of prescribed packs of medication for HIV therapy
  - Details of strength
  - Details of pack size
  - Details of date period of prescription
    - 1. ***Recording of prescribed substitution medication***
- Number of prescribed packs of medication for substitution
  - Details of strength
  - Details of pack size
  - Details of date period of prescription
    - 1. ***Recording of referrals to specialists***
- Date period of referral
- Number of referrals
- Choice of specialist group (selection field)
  - Dermatologist
  - Radiologists
  - Psychiatrist/neurologist
  - Endocrinologists
  - Ophthalmologist
  - Rheumatologist
  - Dentist
  - Cardiologist
  - Nephrologist
    - 1. ***Recording of cooperation with general practitioner***

The cooperation with the general practitioner is recorded in terms of

- Treatment monitoring
- Interferon prescription
- Interferon administration
- Adverse drug reaction management.
  - - 1. ***Recording of incapacity for work***
- Gainful employment yes/no
- Nature and extent of gainful employment
- Highest educational attainment
- Treatment-related sickness periods (days)

The sociodemographic data and information on treatment-related periods of sick leave are taken from the main module, their availability is assured by compulsory fields in the pharmacoeconomic module.

- - - 1. ***Recording of hospitalizations***
- Number of days in hospital associated with the HCV disease or HCV therapy
- Details of reason for admission (as free text)
- Link to the SAE reports

### Recording of adverse events and pregnancies

The following data are collected for recording adverse events:

- Description of the event
- Start and end date
- Severity (mild, moderate, severe)
- Seriousness criteria
- Outcome of the event
- Causal relationship with the treatment
- Therapy

The physician's assessment regarding whether an adverse event is serious is recorded in the case record form.

Recording of pregnancies

At least the following data are collected for recording of pregnancies (pregnancy / lactation, paternal exposure):

- Details of pregnancy and course of pregnancy
- Outcome of pregnancy (fetus)
- Seriousness criteria (fetus)
- Causal relationship with the treatment
- Information on the infant

## Influencing and interfering variables

At baseline, the year of the first diagnosis of hepatitis C, the, hepatitis C genotype, hepatitis C viral load, immune status, blood and liver values and relevant comorbidities are recorded. The clinical course parameters are evaluated taking into account their recorded baseline values. Weight, ethnicity, gender and age are documented at study outset, as these values can represent positive and negative predictive factors. In addition, any deviations in the patient distribution compared to the distribution in previous studies can be recorded and evaluated.

